**7.4 Exercise intensity assessment**

The assessment of exercise intensity in your study is based on the percentage of maximum heart rate. Continuous heart rate monitoring is conducted throughout the exercise session using a Mio heart rate monitor (Mio Alpha II, USA). At the conclusion of the exercise, the average heart rate output is determined. This is done by measuring the heart rate three times for the same individual and calculating the mean value. The percentage of maximal heart rate is calculated using the following formula:

- % of maximal heart rate=(measured heart rate / 220−age)×100%

The target exercise intensity is set to moderate or upper moderate, which corresponds to 60%-80% of the maximum heart rate value.

**7.5 Assessment of sports attendance**

The protocol for tracking attendance in your study is well-defined. Intervention supervisors are responsible for recording attendance at each training session. Participants who engage in the training for less than 20 minutes are marked as absent.

The attendance rate is calculated at the conclusion of the intervention period using the formula:

- % attendance=(number of training sessions attended / total number of training sessions planned)×100%

1. **Measure**

**8.1 Demographics**

For the comprehensive assessment of participants in your study on sarcopenia, the following data should be meticulously collected:

- Demographic Data: This includes the participant’s name, gender, date of birth, education level, weight, height (or BMI), ethnicity, occupation, and contact address.
- General Physical Examination: Vital signs such as heart rate, pulse, respiration, and blood pressure should be systematically recorded.
- Medical and Social History:
- Current Medical History: Document any present health conditions.
- Co-morbidities and Medications: List any concurrent illnesses and current medications.
- Allergies: Note any known allergies.
- Family History: Include any relevant hereditary health issues.
- Smoking and Alcohol History: Record past and present tobacco and alcohol use.
- Additional Relevant Information: Gather details on any falls within the past year, hand dexterity (sharp hands), sleeping habits, hobbies, personality traits, social activities, and other lifestyle factors that may influence the condition.

**8.2 Primary outcome**

The Short Physical Performance Battery (SPPB) is indeed a widely recognized assessment tool for evaluating the physical function of older adults. It encompasses three key components:

- Repeated Chair Stands: This task measures lower body strength by timing how long it takes to stand from a seated position and sit down again, repeated five times.
- Balance Tasks: These tasks assess static balance through three progressively challenging positions—side-by-side stand, semi-tandem stand, and tandem stand—each held for 10 seconds.
- Gait speed: This component evaluates walking speed over a short distance as a measure of gait speed and overall mobility.

Each task is scored individually, and the scores are then aggregated to yield an overall performance score ranging from 0 (indicating the poorest function) to 12 (representing the best function). Higher SPPB scores correlate with better physical function and mobility in older adults.

**Table 1. Simple Physical Performance Battery (SPPB)**

| Test items | | Criteria for judging | score |
| --- | --- | --- | --- |
| Balance test | stand on one foot | Hold on 10s. | 1 |
|  | half-fore-and-aft stance | Failure to hold 10s | 0 |
|  | front-and-back stance | Hold on 10s. | 1 |
| 4 meters walking time | | Failure to hold 10s | 0 |
|  |  | Hold on 10s. | 2 |
|  |  | Hold on 3s to 9.99s. | 1 |
|  |  | Hold on <3s | 0 |
|  |  | Time <4.82s | 4 |
|  |  | Time 4.82s to 6.20s | 3 |
|  |  | Time 6.21s to 8.70s | 2 |
|  |  | Time >8.70s | 1 |
|  |  | unfinished | 0 |
| Repeat 5 sit-up test | Before the test (without hands) | Time <11.20s | 4 |
|  | Repeat 5 times | Time 11.20s to 13.69s | 3 |
|  |  | Time 13.70s to 16.69s | 2 |
|  |  | Time >16.70s | 1 |
|  |  | Takes more than 60s or cannot be completed | 0 |
| Total score | | |  |

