**3.1 Participants**

**3.1.1 Diagnostic criteria**

The diagnostic criteria set forth by the Asian Working Group for Sarcopenia ^[13]^ are as follows:

- A: SMI (Skeletal Muscle Index): This is determined using Bioelectrical Impedance Analysis (BIA) and should be less than or equal to 7.0 kg/m^2^ for males and less than or equal to 5.7 kg/m^2^ for females.
- B: Muscle strength (Handgrip Strength): The strength threshold is less than 28 kg for males and less than 18 kg for females.
- C: Physical performance

6-metre walk: <1.0 m/s

or 5-me chair stand test: ≥12 s

or Short Physical Performance Battery: ≤9

A diagnosis of sarcopenia is confirmed when both criteria A and B or A and C are met. It's important to note that these criteria are specifically tailored to the Asian population and take into account the distinct body composition profiles prevalent in this demographic.

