**10.1 Power calculation**

The prevalence of falls and fractures due to the diminution of muscular mass and function underscores the clinical urgency and grave repercussions associated with sarcopenia. Drawing upon empirical evidence from a preceding trial targeting older adults predisposed to falls ^[14]^, the Short Physical Performance Battery (SPPB) is employed as the primary efficacy index. Utilizing a two-sided test with a power of 90% and a significance level of 5%, the requisite sample size for a single intervention group is deduced to be approximately 36. Accounting for an anticipated dropout rate of 20%, each group necessitates 45 participants diagnosed with sarcopenia.

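### Section 8.2 and Table 1 name different tasks for the first SPPB balance point, so one of the 12 points of the primary outcome is not uniquely defined

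*Combined protocol and SAP*

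**What the plan says.** Section 8.2 describes the SPPB as chair stands, balance tasks and gait speed, with a total from 0 to 12. It lists the balance tasks as "side-by-side stand, semi-tandem stand, and tandem stand", calls them "three progressively challenging positions", and requires each to be held for 10 seconds.

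Table 1, which follows directly, sets out the points. Its three balance items are "stand on one foot", "half-fore-and-aft stance" and "front-and-back stance".

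The score has three uses in the plan:

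- **Primary outcome.** Section 10.1 states that "the Short Physical Performance Battery (SPPB) is employed as the primary efficacy index". Table 2 schedules physical function at weeks 0, 12 and 24.
- **Diagnosis.** Section 3.1.1 includes "Short Physical Performance Battery: ≤9" as one of three alternatives under criterion C.
- **Exclusion.** Section 3.1.3 separately excludes anyone whose SPPB is above 9.

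**The concern.** The first balance item differs in substance between the text and the table. In section 8.2 it is the easiest of three graded positions, so a person who can hold the tandem stand would be expected to earn its point as well. With a one-foot stand in that place the grading breaks: a participant could hold both later stances and still lose the first point.

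The table is the part of the protocol that assigns points, so an assessor working from it would score a task that the text does not include. If some assessors follow the text and others the table, the same physical performance can receive two scores. That adds avoidable measurement error to the primary outcome, although section 9.4 promises standardised methods of data collection. The same point also counts at screening, where the cut-off is 9.

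**Working it through.** No sample-size or test formula applies here. The check is a comparison of the two descriptions, a sum of the points, and the effect of one point on the total.

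**1. Items side by side**

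| Balance item | Section 8.2 | Table 1 | Same task? |
| --- | --- | --- | --- |
| First | side-by-side | one foot | No |
| Second | semi-tandem | half fore-and-aft | Yes, in meaning |
| Third | tandem | front-and-back | Yes, in meaning |

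The row alignment of Table 1 is disturbed in the text available for review. That can move cells, but it does not change the words of a label, and the first label is legible.

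**2. Does the point structure hold?** The item maxima in Table 1 are balance 1 + 1 + 2 = 4, walk 4 and chair stand 4. The total is 4 + 4 + 4 = 12, which reproduces the maximum in section 8.2. The conflict is therefore confined to which task earns the first balance point.

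**3. Effect on one score.** The first balance item carries 1 point. A participant who holds side-by-side but not one foot scores 1 under section 8.2 and 0 under Table 1, so the total falls by 1 of 12. A participant who can do both, or neither, has the same score either way. The reverse case, holding one foot but not side-by-side, is implausible. The shift per assessment is thus 0 or −1, and it can arise at weeks 0, 12 and 24.

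**4. Effect at the cut-off.** Only a person at exactly 10 under section 8.2 who fails the one-foot stand is affected: 10 − 1 = 9. That person then meets the SPPB alternative in section 3.1.1 and is no longer caught by the SPPB exclusion in section 3.1.3. The diagnosis itself changes only for someone with low muscle mass (criterion A) who has no other route, because criteria A and B together suffice and SPPB is one of three alternatives within C. The exclusion has no such alternative route.

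**5. Effect on the comparison between arms.** Let p be the proportion in an arm who hold side-by-side but fail one foot. The shift in that arm's mean is −p, so the between-arm difference moves by the difference in p between arms. The document gives no values for p. The planned difference is 9.83 − 8.39 = 1.44 points (section 4). As assumptions only:

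| p, one arm | p, other arm | Shift in difference | Share of 1.44 |
| --- | --- | --- | --- |
| equal | equal | 0 | 0% |
| 30% | 20% | 0.10 | 0.10/1.44 = 7% |
| 100% | 0% | 1.00 | 1/1.44 = 69% |

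**6. Two smaller faults in the same table.** The repeated-rise task is called a sit-up in Table 1 and a chair stand in section 8.2. A time of exactly 16.70 s has no score: 13.70 to 16.69 s earns 2 points, and the next band starts above 16.70 s.

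**The case against.** The strongest reply is that this is a translation slip with no consequence. The document's English is loose elsewhere: the chair stand is called a sit-up in the same table, and section 4 gives the SPPB a different name. Section 8.2 names the balance sequence explicitly, two of the three items agree, and the points add to 12. The form that assessors actually used is not among the documents. All of this is fair. It means the harm is conditional on assessors having followed Table 1. It does not remove the conflict, because nothing says which description governs, and the table is where the points are assigned.

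A second reply is that both arms share the table and section 6 plans blinded outcome assessment, so a common shift cancels in the comparison. This also stands. A reader might divide the one point by the planned 1.44 and infer that 69% of the treatment effect is at risk. That sets one participant's largest possible loss against a difference between group means. It would be reached only if everyone in one arm and nobody in the other were affected.

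Two further inferences are tempting and lack support. One is that a programme trains single-leg balance directly and so favours its own arm; sections 7.1 and 7.2 name no single-leg stance. The other is that the scores cannot be compared with the 9.83 and 8.39 used for planning; the protocol does not describe the balance items of the cited trial.

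Finally, the document does not itself say that a one-foot stand is harder. That is a judgement from the nature of the task and from side-by-side coming first in a rising sequence.

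**Conclusion.** The inconsistency is real: the text and the only scoring table of the primary outcome name different tasks for the first balance point, and no other section reconciles them. Its size is bounded at 1 of 12 points per assessment, plus a possible crossing of the SPPB cut-off for participants at exactly 10 under section 8.2.

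The consequence rests on two assumptions: that at least some assessors score from Table 1 as written, and that some participants can stand side-by-side but not on one foot for 10 s. If the label is only a translation slip and the side-by-side stand was administered throughout, no score is affected and the remedy is editorial.

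The threat is to validity of the score, agreement between assessors and eligibility. The documents do not show a bias between arms. The point still deserves correction, because a reader cannot tell from the protocol which task produced part of the primary score.

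**What to change.** - In Table 1, name the first balance item *side-by-side stand (10 s)*, in agreement with section 8.2.
- Make sure the case report form carries the same wording.
- Confirm with the assessors which task was administered at screening and at weeks 0, 12 and 24, and record the answer. Flag records only if the one-foot task was used, including any in which the SPPB cut-off decided eligibility.
- In the same edit, change sit-up to chair stand and assign a score to a time of exactly 16.70 s.

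The cost is one corrected table, a check of the form and one query to the assessors. A review of completed records is needed only if that query shows that the one-foot task was used.

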**8.3 Secondary outcomes**

The methodology for assessing the efficacy of the intervention on elderly patients with sarcopenia is comprehensive and multi-faceted, involving the following measures:

- Body Composition Analysis: Utilizing the DBA-510 Body Composition Analyzer, participants' body weight, body water, fat mass, fat percentage, lean body weight, BMI, and segmental muscle mass of the trunk, upper, and lower limbs will be evaluated through bioelectrical impedance analysis.
- Handgrip Strength Measurement: The JAMAR electronic grip strength meter will be employed to gauge upper limb muscle strength. Participants will perform the test standing, with arms at their sides, elbows bent at 90°, and forearms supinated, exerting maximum grip strength. The highest value from four measurements (two per side) will be recorded.
- 6-Meter Walk Test: This test assesses muscle performance by having participants walk 6 meters at their usual pace. The walking speed is calculated based on the time taken to complete the distance. The test is conducted twice, and the average time and speed are noted.
- Cognitive Function Assessment: The 30-item Montreal Cognitive Assessment (MoCA, Changsha version) will be used to measure global cognitive function. This instrument is tailored for Chinese populations and scores cognitive function across multiple domains on a scale from 0 to 30, with higher scores indicating better cognitive function.
- Incidence of Falls Tracking: Participants will maintain a "fall calendar" diary to document any falls and related medical consultations monthly. This includes accidental landings on the floor or ground or collisions with objects. The collection of fall data commences with the first intervention class and continues until the intervention's conclusion or until a participant's withdrawal, death, or loss to follow-up.

1. **Quality control**

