**3.1.5 Elimination criteria**

- Participants who are subsequently found to not fulfill the inclusion criteria after the commencement of the study will be excluded.
- Subjects who decline to participate in the prescribed examination and assessment protocol during the study will be withdrawn.
- Participants demonstrating suboptimal adherence, with cumulative exercise time falling below 80% of the prescribed amount, or those who consume medication that influences muscle or bone metabolism during the study period, will be considered non-compliant and thus removed from the trial.

1. **Sample size**

The prevalence of functional falls and fractures is a significant clinical concern and a severe consequence for patients with sarcopenia, stemming from the progressive loss of muscle mass and function. The Simple Physical Performance Measurement Scale (SPPB) serves as a pivotal efficacy indicator in this context. Drawing from extant literature ^[14]^, a 24-week exercise intervention in elderly patients with a heightened risk of falls yielded an SPPB score of 9.83 ± 1.85 in the experimental group, compared to 8.39 ± 2.52 in the control group. Employing a two-sided test with an alpha level (α) of 0.05 and a power (test efficacy) of 0.9, the calculated sample size for a single group is n = 35.6, which approximates to 36 participants. Consequently, the combined sample size for both groups amounts to 72 individuals. Factoring in a dropout rate of 20%, the total sample size required for this study is 90 cases, equating to 45 participants per group.

1. **Participant**

The proposed study aims to enroll 90 elderly patients with sarcopenia who visited the Hospital of Chengdu University of Traditional Chinese Medicine between July 2022 to August 2023. The process for inclusion involves a meticulous screening of candidates at the outpatient clinic. Potential participants are to be thoroughly informed about the study’s objectives, procedures, and potential risks. Following this educational dialogue, those who meet the study criteria and express a willingness to participate will be asked to provide informed consent and sign the corresponding consent form.

1. **Randomization and Blinding**

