The random allocation sequence was delegated to a specialized statistical analyst, who utilized the SAS 9.4 software (SAS, USA) to generate a series of random numbers ranging from 1 to 90. Subsequently, the analyst enumerated the eligible participants in sequential order of their enrollment and allocated them randomly in a balanced 1:1 ratio to either the Baduanjin exercise intervention cohort—hereinafter referred to as the ‘Baduanjin group’—or the resistance training comparator arm—hereafter denoted as the ‘control group’. The integrity of the randomization sequence was preserved by the study administrator, who remained uninvolved in participant recruitment, outcome evaluation, and statistical analysis. Upon completion of all initial assessments, participants were apprised of their group assignment via telephone.

Due to the nature of the intervention, it was impracticable to blind the study participants. Consequently, blinding was confined to the outcome assessment, data management, and statistical analysis phases. In lieu of explicit group identifiers, the designations ‘A’ and ‘B’ were employed on the case report forms to maintain anonymity. An independent statistical expert, external to the participant cohort, employed SAS software to create the blind base—a table of random numbers—which was subsequently safeguarded by the study administrator. The statistician tasked with data analysis remained uninformed about the specific intervention programs administered to each group. This blinding was only disclosed subsequent to the completion of all statistical analyses.

1. **Interventions**

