**7.1 The Baduanjin Group**

In conjunction with health education initiatives, the Baduanjin training is conducted at a designated time and location. Each session is facilitated by an instructor with a minimum of five years’ experience in teaching Baduanjin. The training adheres to the Baduanjin standards promulgated by the State General Administration of Sports in 2006 ^[15]^. The sequence comprises a preparatory stance followed by a series of ten movements:

- Preparatory Posture
- Holding Up The Sky With Both Hands To Regulate The Sanjiao
- Draw The Bow On Both Sides As If To Shoot A Vulture
- Stretch Arms Asymmetrically To Enhance Spleen And Stomach Function
- Look Back To Treat Five Strains And Seven Impairments
- Sway The Head And Buttocks To Subdue The Heat Fire
- Touch Feet To Strngthen Kidneys And Waist
- Rise Up On Toes And Land On Heels Repeatedly To Cure Disease
- Clench The Fist And Open Eyes Wide To Enhance Vitality
- Closing Posture

The regimen is scheduled three times weekly, with each session lasting 60 minutes. This includes 15 minutes for warm-up activities, 30 minutes dedicated to the Ba Duan Jin exercises, and 15 minutes for cool-down activities, spanning a total duration of 24 weeks.

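### The fall definition in section 8.3 admits collisions without a fall, so reported fall incidence can include events that are not falls

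*Combined protocol and SAP*

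**What the plan says.** Section 8.3 lists falls, under the label "Incidence of Falls Tracking", as one of five secondary measures. Participants keep a calendar-style "diary to document any falls and related medical consultations monthly". The next sentence says what is covered: "This includes accidental landings on the floor or ground or collisions with objects". On timing, "The collection of fall data commences with the first intervention class", and collection runs until the programme ends or the participant leaves the study, dies or is lost. Section 7.1 describes the programme as "spanning a total duration of 24 weeks", and section 7.2 gives the comparator the same length.

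No other definition of a fall appears:
- Section 8.1 asks at baseline about falls in the past year and does not mention collisions.
- Section 9.4 has records verified for completeness and accuracy. It does not provide for classifying events.
- Section 10.2 describes GEE models and a two-sided 5% level. It names no rate ratio, count model or person-time offset for falls.
- Section 6 states that participants could not be blinded.

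Section 4 opens with "The prevalence of functional falls and fractures is a significant clinical concern and a severe consequence for patients with sarcopenia" but bases the sample size on SPPB.

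**The concern.** The outcome is labelled as falls, yet the sentence describing it offers two alternatives, and the second does not require the participant to go down. Taken as written, knocking into a table and staying on one's feet is recordable. The checks in section 9.4 would not catch it, because such an entry is complete and accurate by the plan's own terms.

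Two things are at stake. The first is the meaning of the reported figure: a fall incidence that contains non-falls is too high, and it may not match the falls history taken at baseline. The second is the comparison between arms: a mixture of two event types estimates a mixture of two effects. If the arms do not differ on collisions, the mixed ratio lies closer to 1 than the ratio for falls. Since the comparator is itself an exercise programme, a ratio near 1 could be misread as the two programmes being alike for falls.

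**Working it through.** The documents give no fall rate, rate ratio, collision share or power for falls, so there is no figure of the plan's own to reproduce. The inputs are of two kinds.

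*From the documents:* 45 participants per group (section 4: "the total sample size required for this study is 90 cases, equating to 45 participants per group"), 1:1 allocation (section 6), 24 weeks (7.1 and 7.2) and two-sided 5% (10.2).

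*Assumed, shown over ranges:* c, the share of control-arm diary events that are collisions without a fall; the true fall ratio RR_fall; the collision ratio RR_coll; and the fall rate. The use of a ratio is also an assumption, since the plan names none.

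**Step 1. Inflation of incidence.** If a share c of control-arm events are not falls, the recorded control-arm count is 1/(1 − c) times the true fall count.

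**Step 2. Ratio when collisions are unrelated to arm (RR_coll = 1).** Recorded ratio = (1 − c) × RR_fall + c × RR_coll. For example, at c = 25% and RR_fall = 0.70: 0.75 × 0.70 + 0.25 = 0.775.

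| c | Control-arm inflation | True 0.50 recorded as | True 0.70 recorded as |
|---|---|---|---|
| 10% | 1.11 | 0.55 | 0.73 |
| 20% | 1.25 | 0.60 | 0.76 |
| 25% | 1.33 | 0.625 | 0.775 |
| 50% | 2.00 | 0.75 | 0.85 |

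**Step 3. Ratio when collisions are not unrelated to arm (c = 20%).**
- RR_fall = 0.50, RR_coll = 0.50: 0.8 × 0.50 + 0.2 × 0.50 = 0.50, no change.
- RR_fall = 0.50, RR_coll = 0.3: 0.40 + 0.06 = 0.46, away from 1.
- RR_fall = 1, RR_coll = 0.3: 0.80 + 0.06 = 0.86, an apparent effect where falls show none.
- RR_fall = 1, RR_coll = 1.5: 0.80 + 0.30 = 1.10, an apparent effect in the other direction.

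The same arithmetic covers differential reporting: if participants in one arm log collisions more readily, the recorded collision ratio moves off 1 even when the true one is 1.

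**Step 4. Difference scale.** Assume 1 fall per person-year in the control arm, RR_fall = 0.70, and the same collision rate of 1/3 per person-year in both arms (c = 25%). Recorded rates are 1.333 and 1.033. The ratio is 0.775, but the difference is −0.30, the same as for falls alone (0.70 − 1.00).

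**Step 5. Power, for context.** Person-time per arm with full follow-up is 45 × 24/52 = 20.77 years. Power is Φ(|ln ratio| / √(1/E₀ + 1/E₁) − 1.96) for Poisson counts with expected events E₀ and E₁. Assume 1 fall per person-year and RR_coll = 1.
- RR_fall = 0.50, c = 0: E₀ = 20.77, E₁ = 10.38, power about 45%.
- RR_fall = 0.50, c = 20%: E₀ = 20.77/0.8 = 25.96, E₁ = 0.60 × 25.96 = 15.58, power about 36%.
- RR_fall = 0.70, c = 0: E₀ = 20.77, E₁ = 14.54, power about 18%.
- RR_fall = 0.70, c = 20%: E₀ = 25.96, E₁ = 19.73, power about 15%.

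**The case against.** The strongest reply is that the sentence only illustrates the falls mentioned just before it, and that the collision clause means falling against an object. That reading is possible. It is not what the words say, though, and a clarifying sentence is needed under either reading.

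A reader might infer several stronger claims that the documents do not support:
- *That the clause pulls any rate ratio towards 1.* Step 3 shows no change when collisions respond as falls do, and movement away from 1 when they respond more. On the difference scale, equal contamination leaves the expected contrast unchanged and only adds noise (step 4). The plan commits to neither scale for falls.
- *That neither programme is meant to affect collisions.* Nothing in the documents says so, and the primary outcome measures balance, gait and leg strength, which could bear on collisions.
- *That participants will apply the wording literally.* The diary page is not in the documents, and nothing shows that this sentence is printed on it.
- *That the clause hides a real difference.* No fall rate or effect is given. On the assumptions of step 5, a true ratio of 0.70 has about 18% power even with no collisions, so small numbers are the main obstacle.
- *That falls are the trial's central justification.* Section 4 cites falls to motivate SPPB, and the purposes in section 2 are framed around SPPB, quality of life and safety.

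These points limit what can be said about direction and importance. They do not remove the defect: the stated rule lets non-falls into a falls outcome.

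**Conclusion.** The point stands as a minor flaw in a stated definition. As worded, section 8.3 counts collisions without a fall, and nothing later in the plan takes them out. Fall incidence is inflated whenever one is logged: by a factor of 1.11 to 2.00 in the control arm if such collisions are 10% to 50% of its events.

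Dilution of a ratio is conditional. It requires the collision ratio to be nearer 1 than the fall ratio. With collisions wholly unrelated to arm, a true 0.70 is recorded as 0.73, 0.78 or 0.85 at shares of 10%, 25% or 50%. If collisions respond to training, or are reported differently by unblinded participants, the bias can run either way. All shares, rates and ratios here are assumptions.

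Severity is low because falls are a secondary outcome and the sample size was not set for them.

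**What to change.** In section 8.3 and on the diary page, count an event as a fall only when the participant unintentionally comes to rest on the floor, ground or other lower level, or falls against an object. Give collisions without a fall their own line on the diary and state that they do not enter the falls outcome.

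The cost is one sentence in the protocol and one line on the diary. No visit, treatment or sample size changes. The downside is fewer counted events. The collision records are kept and can be described separately.
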